## Abstract

**Background:**

Over 12,000 individuals suffer a spinal cord injury (SCI) annually in the United States, necessitating long-term, complex adjustments and responsibilities for patients and their caregivers. Despite growing evidence that family education and support improves the management of chronic conditions for care recipients as well as caregiver outcomes, few systematic efforts have been made to involve caregivers in psycho-educational interventions for SCI. As a result, a serious gap exists in accumulated knowledge regarding effective, family-based treatment strategies for improving outcomes for individuals with SCI and their caregivers. The proposed research aims to fill this gap by evaluating the efficacy of a structured adaptation of an evidence-based psychosocial group treatment called Multi-Family Group (MFG) intervention. The objective of this study is to test, in a randomized-controlled design, an MFG intervention for the treatment of individuals with SCI and their primary caregivers. Our central hypothesis is that by providing support in an MFG format, we will improve coping skills of persons with SCI and their caregivers as well as supportive strategies employed by caregivers.

**Methods:**

We will recruit 32 individuals with SCI who have been discharged from inpatient rehabilitation within the previous 3 years and their primary caregivers. Patient/caregiver pairs will be randomized to the MFG intervention or an active SCI education control (SCIEC) condition in a two-armed randomized trial design. Participants will be assessed pre- and post-program and 6 months post-program. Intent to treat analyses will test two a priori hypotheses: (1) MFG-SCI will be superior to SCIEC for SCI patient activation, health status, and emotion regulation, caregiver burden and health status, and relationship functioning, and (2) MFG will be more effective for individuals with SCI and their caregivers when the person with SCI is within 18 months of discharge from inpatient rehabilitation compared to when the person is between 19 and 36 months post discharge.

**Discussion:**

Support for our hypotheses will indicate that MFG-SCI is superior to specific education for assisting patients and their caregivers in the management of difficult, long-term, life adjustments in the months and years after SCI, with increased efficacy closer in time to the injury.

**Trial registration:**

ClinicalTrials.gov NCT02161913. Registered 10 June 2014.

## Background

In the United States, an estimated 276,000 individuals currently live with spinal cord injuries (SCIs) [1]. The vast majority of SCIs are the result of unexpected events (i.e., vehicular accidents, falls, acts of violence, and accidents that occur during sports and recreation) that immediately, dramatically, and permanently change the lives of those who experience them [2]. Over half of the individuals who experience SCI are healthy [3] and employed [4] at the time of their injuries. The vast array of loss that ensues is life-shattering and includes loss of mobility, loss of functional abilities, changes in sensory and autonomic functioning, multisystem impairment, risk of serious secondary complications, and decrease in life expectancy [4, 5]. Not only are those who experience SCI largely young–between the ages of 15 and 35 years–they are most frequently single young men [3, 4, 6] who find themselves unable to maintain employment [4] as a result of related disability [7] and suddenly dependent upon others for their care [8]. Physical limitations related to their injuries also limit their social interaction and interfere with their ability to perform social roles [9, 10]. Each of these stressors contributes to extremely high levels of psychological distress and morbidity [8], including increased risk for substance abuse [11], decreased life satisfaction [12], decreased social integration, and increased loneliness [9, 10].

The vast majority of those who experience SCI are sent home after discharge from the hospital [4]. Family members often find themselves in the role of caregivers, serving as advisors, educators, advocates, and prevention / management specialists concerning health complications, as well as providing financial support [5]. While such support has been described as indispensable for individuals with SCI [5], it significantly strains family members in these positions [13–15]. Caregivers often report chronic health problems, feelings of frustration, isolation, guilt, and resentment toward their injured family member [16]; spouses of individuals with SCI have been found to self-report even higher levels of distress than with the person with SCI [17]. There is an obvious need for psychologically based interventions aimed at improving the health status and quality of life for individuals with SCI and those who care for them [8].

Decades of research and meta-analytic reviews have demonstrated that the education and involvement of caregivers in the treatment of persons with other chronic conditions (e.g., severe mental illness) results in improved rehabilitative and community outcomes relative to those receiving individual treatment or treatment as usual [18–20]. When used with schizophrenia and traumatic brain injury (TBI), one such approach that engages care recipient and caregiver in co-treatment, termed Multi-Family Group (MFG) psycho-education, has been found to improve the management of these conditions and improve caregiver outcomes as well [21–24]. However, few systematic efforts have been made to involve caregivers in psycho-educational interventions designed to improve adjustment to SCI. As a result, a serious gap exists in accumulated knowledge regarding effective, family-based treatment strategies for improving outcomes for individuals with SCI and their caregivers. This study aims to fill this gap by evaluating the efficacy of a structured adaptation of an evidence-based group treatment for SCI. This psychosocial intervention, MFG for SCI (MFG-SCI), builds on earlier work by [name] and colleagues [21].

The purpose of this study is to rigorously test the previously developed MFG intervention for persons with SCI and their primary caregivers. We will recruit individuals with SCI who have been discharged from inpatient rehabilitation within the previous 3 years and their primary caregivers. The MFG intervention will be compared to an active control condition (SCIEC) in a two-armed randomized trial design. We will test the following hypotheses in the proposed study: 1) The MFG intervention relative to the SCIEC condition will result in greater improvement in quality of life, health activation, and health status and psychological functioning among individuals with SCI; it will also result in reduced caregiver burden among informal caregivers, as well as improved relationship quality. 2) The MFG intervention will be shown to be more effective for individuals with SCI and their caregivers when the patient is within 18 months of discharge from inpatient rehabilitation (e.g., sub-acute phase of adjustment to injury), compared to when the patient is between 19 and 36 months post discharge from inpatient rehabilitation (e.g., chronic phase of adjustment to injury).

## Methods and design

We will randomize 32 outpatients with SCI and their caregivers to a 9 month MFG intervention (MFG-SCI, *n* = 16 pairs) or to an SCI education control condition (SCIEC, *n* = 16 pairs) of the same duration. Over time, each condition will have 4 to 5 cohorts of 3 to 5 couple pairs. Participants will receive the different treatments at a single medical rehabilitation hospital. All participants will provide written informed consent prior to participation. The SCIEC condition will be based on the 4th Edition of the book titled: *Yes, you can: A guide to self-care for persons with spinal cord injury* [25]. The content will be taken from four sections of the book and will be covered in 16 bi-monthly sessions: 1. How SCI affects your body; 2. Maximizing your function; 3. Coping and Living with SCI; and 4. Staying healthy with SCI. The study will employ a two-arm randomized intervention-control design with repeated measures of outcomes across time. Depending on characteristics of individuals with SCI who consent to participate, we will stratify participants on time since injury (≤18 months post discharge vs. 19–36 months) and location/severity of the SCI (American Spinal Injury Association [ASIA] Classification system) and randomize to the two conditions, rigorously assessing outcomes of those with SCI and their caregivers. The SCIEC intervention will provide SCI management information in a didactic format, but it will not include the group problem-solving or structured social support afforded by MFG over the same 9-month period. Each of the clinicians will be provided a manual for didactic components of the intervention; in addition, they will receive bi-weekly supervision by the PI. For all participants, we will continue to measure outcomes after completion of the 9-month intervention period in order to assess durability of outcomes.

Eligibility criteria for individuals with SCI will include: having an SCI (quadriplegia or paraplegia) due to an acquired injury with complete or incomplete lesion as defined by ASIA; discharge from inpatient rehabilitation within the previous 3 years; being age 16 years or older; having a mobility impairment as the result of the SCI; living in the community in a non-group setting after injury; planning to remain in the geographic area for at least 12 months; and competency in English. Dyads will be excluded if the primary caregiver or person with SCI has a terminal illness with life expectancy of less than 12 months; is in active treatment for cancer; is blind or deaf; or has a moderate to severe cognitive impairment (defined at screening as a score on the Short Portable Mental Status Questionnaire > 4 errors).

Eligibility criteria for primary caregivers will include provision of instrumental or emotional support for a spouse, relative, partner, or friend with SCI; having regular contact with the individual with SCI (at least a minimum of 2 h face-to-face contact per week); living with or near the individual with SCI; being age 18 or over; having a telephone; planning to remain in the geographic area for at least 12 months; and competency in English.

### Outcome measures

Individuals with SCI and their caregivers will be assessed pre- and post-treatment and 6 months post-treatment (see Table 1). Outcomes will be assessed with psychometrically validated quantitative measures for persons with SCI and caregivers. We will also measure the quality of the dyad’s relationship. Qualitative focus groups will be conducted with all participants at the end of the treatment periods to uncover participant perceptions of overall group experience, how useful it was, suggestions for improvement, and information and/or coping skills they learned to support rehabilitation or care giving.

**Table 1 Tab1:** SCI and caregiver assessments and measurement schedule

		Pre-treatment	Post-treatment	6-months
SCI Patient Assessments				
Patient Activation				
	**Patient Activation Measure (PAM)**	X	X	X
Emotion Regulation/Interpersonal Skills				
	AX Scale (anger expression)	X	X	X
	Duke Social Support Index (use of supports)	X	X	X
Mental Health/Health Behavior				
	CES-D-10 (depression)^a^	X	X	X
Neuropsychological				
	Mini-Mental Status Examination	X		
Caregiver Assessments				
Caregiver Burden/Health				
	**Caregiver Burden Inventory**	X	X	X
	**CES-D-10 (depression)** ^**a**^	X	X	X
Dyad Functioning (administered to patient and care partner)				
	F-COPES	X	X	X

Bolded measure indicates primary outcome measure

^a^covariate in analyses

### SCI patient assessments

The Patient Activation Measure (PAM) [26] will be used to assess our primary quality of life outcome: health/patient activation. The PAM will measure the degree of individual’s knowledge, confidence, and skill to participate in self-management [26]. A higher degree of patient activation has been associated with better health outcomes for adults with chronic conditions [27–30]. Two measures will be used to assess our secondary outcomes of anger-expression and social support (i.e., change in the person with SCI’s use of adaptive social behaviors needed for effectively coping with SCI): the Anger Expression Scale (AXS) [31] will measure anger management including anger-in (suppression of angry feelings), anger-out (expression of anger towards property or people) and anger control (the frequency of attempts to control expressions of anger). The Abbreviated Duke Social Support Index (ADSSI) [32] will be used to measure both subjective support and social network interactions. We will also evaluate the presence and severity of depressive symptoms as these may influence benefits derived from treatment. The 10-item form of the widely-used, reliable Center for Epidemiologic Study of Depression (CESD-10) [33] will assess level of current depressive symptoms.

### Caregiver assessments

The Caregiver Burden Inventory (CBI) [34] will evaluate caregiver burden in four areas: physical, social, emotional and time dependence burden. The CESD-10 will be used to evaluate depressive symptoms during the past 6 months.

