## Discussion

There is currently a knowledge gap concerning how to best help individuals with SCI incorporate effective management strategies into their everyday lives to support coping and functional independence. There is also a paucity of individualized educational and support services for families living with the consequences of SCI. This project will address this gap by conducting a randomized, controlled study to evaluate the effectiveness of the MFG intervention tailored for persons with SCI and their caregivers. Group members with SCI and their caregivers will be provided information about how SCI affects the body and how to maximize adjustments and functioning. They will also learn guidelines for coping, living, and staying healthy after experiencing SCI. Participants will be taught self-care strategies related to SCI, given practice in solving problems related to SCI, and have the opportunity to exchange experiences and coping strategies with other care dyads over an 8 to 9 month period. While the content of the sessions will be guided by set topics, the problem-solving foci will also be informed by information provided by participants during the initial individual ‘joining’ sessions and throughout the MFG treatment. If study outcomes support our hypotheses showing superior efficacy for MFG-SCI vs. SCIEC, MFG implementation could potentially improve the quality of life for many persons with SCI and their caregivers.

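### The CES-D-10 has two conflicting time frames, and the 6-month one falls on the caregiver version, a primary outcome, where it would look back over most of treatment

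*Protocol article*

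**What the plan says.** Under Caregiver assessments, the protocol article states: "The CESD-10 will be used to evaluate depressive symptoms during the past 6 months". Under SCI patient assessments, the same 10-item scale "will assess level of current depressive symptoms". The article gives no reason why the two members of a dyad should answer over different periods.

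In Table 1 (Outcome measures) the caregiver CES-D-10 is in bold, and the key reads "Bolded measure indicates primary outcome measure". The same row carries a footnote reading "covariate in analyses", so the table gives the measure two roles. The patient CES-D-10 has the footnote but is not bold.

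On timing, "Individuals with SCI and their caregivers will be assessed pre- and post-treatment and 6 months post-treatment". Methods and design gives a 9-month intervention, and the Discussion gives 8 to 9 months. Overview of the MFG intervention describes three sequential phases, of which the last is 6 months of group meetings (12 sessions).

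**The concern.** A post-treatment assessment is meant to show how participants are when treatment ends. The General analytic approach models it as a separate time point, and Tests of specific study hypotheses relies on the interaction of group with time of measurement. A score that asks about the past 6 months, taken at the end of a 9-month programme, describes caregivers during treatment. Because the group meetings form the last phase, the window would span essentially all of them, including the early sessions, when little of the skills training has taken place.

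At stake is the size of the post-treatment contrast on a primary outcome: any gradual build-up of benefit would make it look smaller than it is. The article states a recall period, and that period conflicts with the one stated a paragraph earlier. This is therefore a contradiction in the text, not a detail left to a fuller document.

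**Working it through.** **1. Share of treatment inside the window.** Inputs: 6-month look-back (Caregiver assessments); treatment of 9 months (Methods and design) or 8 to 9 months (Discussion).
- 6/9 = 67%
- 6/8 = 75%

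**2. Dilution of the post-treatment effect.** The documents give no time course, so these are assumptions. The factor is the mean of the assumed effect curve over the window, divided by its value at the end of treatment. It also assumes that respondents report an unweighted average over the window.
- Linear build-up over 9 months, window months 3 to 9: ((3 + 9)/2)/9 = 0.67
- Linear build-up over 8 months, window months 2 to 8: ((2 + 8)/2)/8 = 0.63
- Linear build-up over the last 6 months only: (0 + 1)/2 = 0.50
- Effect complete before the window opens: 1.0

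**3. The protocol's own power figures.** Inputs from Power calculations: 16 dyads per group, effect size .6, two-sided alpha 0.01, correlation among repeated measures 0.2, three assessments. The effect-size metric is not named. With .6 read as Cohen's f, the test of the group main effect averaged over three waves has noncentrality λ = N f² / [(1 + 2ρ)/3] on (1, N − 2) degrees of freedom, where (1 + 2 × 0.2)/3 = 0.467.
- N = 32, f = .6: λ = 32 × 0.36/0.467 = 24.7, power 98.3% (stated 97%)
- N = 28, f = .6: λ = 28 × 0.36/0.467 = 21.6, power 96.1% (stated 95%)
- N = 28, f = .5: λ = 28 × 0.25/0.467 = 15.0, power 85.2% (stated 87%)

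All three are within 2 points. Read as a standardized mean difference, .6 gives 41% at N = 32 and does not reproduce the stated figure.

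**4. Power with only the post-treatment wave diluted.** Suppose the post-treatment and follow-up effects are otherwise equal. The average effect is then multiplied by (k + 1)/2, where k is the dilution factor. The multiplier is the same if a zero baseline effect is included in the average. With N = 32:
- k = 0.67: f = .6 × 0.833 = .50, λ = 17.1, power 91%
- k = 0.50: f = .6 × 0.75 = .45, λ = 13.9, power 83%
- k = 1: f = .6, power 98%

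**5. Upper bound on the loss.** If the same factor were applied to the whole effect, f would be .40 (λ = 11.0, power 71%) or .30 (λ = 6.2, power 41%).

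**The case against.** The strongest reply is that the 6-month phrase is a slip in a condensed article. The article says it uses validated measures, names one 10-item form, and does not show the caregiver questionnaire. If caregivers complete the same form as patients, nothing is diluted and the defect is editorial. That may well be so, but the documents do not settle it, and the sentence as it stands fixes a different window for a primary outcome.

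A second reply is that the dilution figures rest on an assumed time course and an assumed way of answering. This stands. An effect already complete when the window opens loses nothing, and one that peaks early and then wanes would not be diluted in this way.

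Three stronger readings may tempt a reader, and the documents do not support them:
- **Power falls to 71% or 41%.** This needs dilution at every wave. At the 6-month follow-up the look-back contains only time after treatment. It averages over that interval, but it does not mix in treatment months.
- **The test of hypothesis 2 is biased.** Eligibility sets no minimum time since discharge, so the baseline window can reach into the inpatient stay for dyads discharged less than 6 months earlier, all of them in the 0–18 month group. Such a shift affects both randomized arms and largely cancels in the arm contrast within that group. It could touch the interaction of time since inpatient treatment with time of measurement, but that term does not compare arms.
- **Patient and caregiver depression cannot be compared.** Each outcome is modelled separately, and no planned analysis makes that comparison.

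**Conclusion.** The contradiction is real and falls on a measure marked as a primary outcome, whose role is itself blurred by the covariate footnote. If the 6-month window is used, the post-treatment caregiver score covers 67% to 75% of treatment instead of its end.

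The consequence for the effect is conditional. Under gradual build-up and simple averaging by respondents, the post-treatment effect appears at about 50% to 67% of its end-of-treatment value, and at 100% if it is complete before the window opens. With only that wave affected, power on the protocol's own model falls from about 98% to between 83% and 91%. The figures of 71% and 41% are an upper bound on the loss. All of these power figures depend on reading .6 as Cohen's f, which the protocol does not state. The point deserves correction because it concerns a primary outcome and is cheap to resolve, not because a large loss has been shown.

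**What to change.** In Caregiver assessments, replace the 6-month phrase with the current-symptom recall period of the validated form used for patients. State that period explicitly in both sections, since the word current alone does not fix a window. Apply it to both dyad members at all three assessments, and check that the caregiver form carries the same instruction.

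If the form already does so, the cost is one phrase. If the form carries a 6-month instruction, it has to be changed before use, and scores already collected under that window cannot be converted. Neither case needs extra data collection.

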### Dyad functioning

The Family Crisis Oriented Personal Evaluation Scales (F-COPES) [35] assesses family-level coping including use of social/spiritual support, reframing negative events, and mobilizing the family to acquire/accept help. The F-COPES has been widely used with internal consistency reliability ranging from .82 to .89 [36]. The F-COPES will allow us evaluate, on an exploratory basis, whether improved dyad functioning is mediated by improved coping and will be administered to both dyad members.

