### General analytic approach

Preliminary analyses will include inspection of descriptive statistics and features of the data to determine whether data transformations for non-normal data are necessary. We will initially test whether baseline characteristics of the study population (e.g., age, sex, race, neurological level, extent of lesion) and other variables known to be related to the primary outcomes are comparable between the two treatment groups using independent t-tests or Wilcoxon rank-sum tests for continuous variables, and chi-square or Fisher’s exact tests for categorical variables. Groups will be considered imbalanced on variables that differ at *p* < .10, and all such imbalanced baseline prognostic factors will be included in primary analyses as covariates. We intend to measure the primary and secondary outcomes described in Table 1 at three time points for each participant (SCI patient and caregiver). Because repeated measurements on individual subjects tend to be correlated and, in some cases, the number and intervals of time between observations may vary among subjects, we will analyze each outcome measure with a general linear mixed model (GLMM) for longitudinal (repeated measures) data by modeling for 3 independent variables: Group (MFG-SCI vs. SCIEC), Time Since Inpatient Treatment (0–18 months vs. 19–36 months post-treatment), and Time of Assessment (pre-treatment, post-treatment, and 6-month follow-up) with covariates represented in the analyses as necessary, and individual subject variables will be simultaneously modeled as random effects. GLMM will account for dependence in repeated measures and accommodate correlated errors, unequal correlations among time points, unbalanced data resulting from missing data points, and unequal intervals between testing occasions. All principal analyses will be conducted based on the intention-to-treat principle in which any participant randomized to a treatment arm remains in it regardless of adherence to or completion of treatment. We will measure level of participation and conduct a sensitivity analysis that assesses the stability of the conclusions from the intention-to-treat analysis against an available-case analysis that considers only data from fully-adherent participants in a General Linear Model (GLM) repeated measures analysis of variance (RMANOVA). With multiple time points and variables representing outcomes at both the individual and caregiver levels, the planned analyses involve multiple comparisons, which increases likelihood that any single outcome will be found to be statistically significant based on chance alone. In order to minimize this risk, we have carefully selected a limited number of outcomes and clearly designated primary and secondary outcomes. Accordingly, we will also employ a more stringent observed type I error criterion (*p* = .01) than the typical .05 criterion in order to buffer against potential inflation of Type I errors due to multiple tests being performed in both the GLMM and RMANOVA.

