### Power calculations

No studies comparing MFG to a control condition in an SCI population exist from which to estimate power. Therefore, we have used a recent trial that included [name] as a co-investigator implementing MFG with survivors of TBI and their families [24]. Significant decreases were reported in TBI patient anger-expression, social support, and occupational activity, with caregivers reporting significantly decreased caregiver burden; all *p*’s < .05. Effect sizes across measures ranged from .6 to 1.0. The proposed study will be powered to determine whether the MFG-SCI is superior to the SCIEC control condition in 2 × 2 × 3, group-by-time since inpatient rehabilitation (0–18 months post-inpatient rehab vs. 19–36 months) by measurement time (baseline, post-treatment, 6-month follow-up) analyses of variance with repeated measures on the second factor. We have elected to estimate statistical power for the more conservative RMANOVA than for the more liberal GLMM procedure in order not to overestimate power. Given the lower bound effect size of .6, a 2-sided type I error rate of 0.01 [24], 1 degree-of-freedom for each between-groups comparison and 2 degrees-of-freedom for the repeated measures main effect, and an estimated correlation among repeated measures of 0.2, at a sample size per group of 16 (32 total dyads), the power to establish superiority of the intervention over the control condition is estimated to be 97 % across the primary and secondary endpoints for SCI patients and caregivers. If we were to lose four dyads to attrition, reducing number of dyads to 28 (14 per group), statistical power given the parameters above would be 95 %. Additionally, at a more conservative effect size of .5, at a sample size of 28, we would still have 87 % power to detect a main effect among groups. Thus, we have good power to detect a medium to large effect size even with a moderate degree of attrition. All power calculations were made with PASSv11.

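### If both dyad members' F-COPES reports enter one model, random effects for individuals alone do not hold the .01 level for the Group main effect

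*Protocol article*

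**What the plan says.** - **Unit randomised.** The Abstract and the Methods and design section randomise patient/caregiver pairs, so both members are always in the same arm.
- **One outcome, two respondents.** Table 1 gives F-COPES a single row under the heading "Dyad Functioning (administered to patient and care partner". The Dyad functioning section describes it as a measure of coping at family level that "will be administered to both dyad members". By contrast CES-D-10, which both members also answer, has two rows in Table 1, one per role.
- **Model.** The General analytic approach plans one general linear mixed model per outcome measure. Its factors are group, time since inpatient treatment and time of assessment, and "individual subject variables will be simultaneously modeled as random effects". The dependence it says it handles is that of repeated measurements. Neither the dyad nor respondent role is named as a model term.
- **Error level.** To guard against multiple testing, "we will also employ a more stringent observed type I error criterion", set at .01 for both the mixed model and the repeated measures ANOVA. The power section likewise uses "a 2-sided type I error rate of 0.01".
- **Standing of the outcome.** F-COPES is not bolded as primary in Table 1, and its use for mediation is called exploratory. It is, however, the only dyad-functioning instrument listed, and relationship functioning is part of hypothesis 1.

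**The concern.** A person-level random effect captures the correlation of one person's answers over time. It does not capture agreement between two people describing the same family. Because pairs are randomised whole, positive agreement makes the arm difference more variable than a model of 64 unrelated people assumes. The standard error is then too small, and a false claim of better dyad functioning is more likely than .01. The plan relies on that strict level as its protection against multiplicity.

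If the two reports are instead modelled separately, the level holds in each test. The single dyad outcome then yields two results that may disagree, and the article does not say which one answers the relationship-functioning part of hypothesis 1.

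**Working it through.** **Step 1. Which unit does the plan's power figure count?** The inputs are in the Power calculations section: effect size .6 ("Given the lower bound effect size of .6"), 16 dyads per group, two-sided .01, M = 3 time points, and correlation over time ρ = 0.2. For the between-group F test of a repeated measures ANOVA, with N units and effect size read as Cohen's f:

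λ = N·f²·M / (1 + (M − 1)ρ), with 1 and N − 2 degrees of freedom.

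| N | f | λ | Power | Stated |
|---|---|---|---|---|
| 32 | .6 | 32 × .36 × 3 / 1.4 = 24.7 | 98.3 % | 97 % |
| 28 | .6 | 28 × .36 × 3 / 1.4 = 21.6 | 96.1 % | 95 % |
| 28 | .5 | 28 × .25 × 3 / 1.4 = 15.0 | 85.2 % | 87 % |

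All three come within 2 points with N = dyads. With N = 64 people the first row would exceed 99.9 %. Reading .6 as a standardised mean difference (f = .3) gives 41 % at N = 32 and 80 % at N = 64, and neither matches. The power calculation therefore counts dyads and does not treat 64 reports as independent.

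**Step 2. Group main effect if both reports are pooled.** Let r be the correlation between the two members' reports averaged over time. The article gives no value, so r = 0.2 to 0.6 is an assumption. With two members in the same arm, the true variance of the arm difference is 1 + r times the modelled one:

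- actual size = 2·(1 − Φ(2.576 / √(1 + r)))
- standard error shortfall = 1 − 1/√(1 + r)
- effective number of people = 64 / (1 + r)

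| r | 2.576/√(1+r) | Actual size | Simulated size, 16 dyads per arm | SE too small by | Effective people |
|---|---|---|---|---|---|
| 0.2 | 2.351 | .019 | .018 | 8.7 % | 53 |
| 0.4 | 2.177 | .029 | .030 | 15.5 % | 46 |
| 0.6 | 2.036 | .042 | .044 | 20.9 % | 40 |

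The simulations used 200,000 trials per value. At r = 0 the size is .010. Over a wider range it runs from .014 at r = 0.1 to .058 at r = 0.8. With the dyad mean as the unit, it stays at about .010 at every r.

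**Step 3. Group-by-Time if both reports are pooled.** This test uses change within persons, so a stable level common to the pair cancels. The simulations used 40,000 balanced trials per setting, with ρ = 0.2:

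| Share of occasion-level variance common to the pair | Size at nominal .01 |
|---|---|
| 0 (stable level shared only) | .010 |
| 10 % | .015 |
| 20 % | .021 |
| 30 % | .028 |
| 50 % | .047 |

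**Step 4. Separate models by respondent.** Each model then holds one person per dyad, so the person effect is also the dyad effect. Size is .010 per test with respect to pairing.

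**The case against.** The strongest objection is that pooling is nowhere stated. A reader might infer that the plan does count 64 reports as independent and that the .01 level is therefore lost. The documents do not support that. The analysis section speaks of measuring each participant and of outcomes for both kinds of respondent, which also fits separate patient and caregiver models. The sample-size figures count pairs ("reducing number of dyads to 28 (14 per group" after attrition), and Step 1 confirms that the power calculation does too. The error claim is therefore conditional on pooling.

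Three further objections carry weight.

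- **The test of improvement.** Hypothesis 1 in the Background concerns greater improvement, which the Group-by-Time test addresses more directly. That test is unaffected by a shared stable level. The inflation in Step 2 belongs to the Group main effect, which the article also plans to test and is the effect it powers.
- **An incomplete remedy.** A dyad intercept alone would not protect Group-by-Time where occasion-level deviations are shared, so the remedy has to cover both.
- **Limited reach.** F-COPES is not a primary outcome.

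It can also be said that a condensed article leaves such detail to an analysis plan. That holds for scoring rules. It answers this point less well, because the article does name the random effects, and those do not fit an outcome with two respondents per randomised unit. The CES-D-10 rows show that Table 1 separates outcomes by role where that is meant, and F-COPES is not so separated.

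**Conclusion.** The point holds in conditional form. Read literally, Table 1 and the General analytic approach give one F-COPES model with person-level random effects only. In that model the nominal .01 Group main-effect test has an actual size of about .019 to .042, for an assumed within-dyad correlation of 0.2 to 0.6. Group-by-Time is inflated only if occasion-level deviations are also shared within pairs, which is a further assumption. Under separate models the level holds per test, and what remains is one dyad outcome with two answers.

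The reach is limited to the only dyad-functioning instrument behind the relationship-functioning part of hypothesis 1. The Patient Activation Measure and the Caregiver Burden Inventory each have one respondent per dyad and are not touched. The change is worth making because it costs little and settles both readings.

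**What to change.** State that F-COPES is analysed at dyad level, in one of two ways:

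1. use the mean of the two members' scores at each time point as the outcome, with the dyad as the subject; or
2. fit both reports jointly, with respondent role as a fixed factor and a dyad covariance that includes a shared level (dyad) and shared occasion-level deviations (dyad-by-time).

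In either case, take the dyad-level arm comparison as the dyad-functioning result and report patient and caregiver estimates alongside. The joint model is the easier choice when one member's report is missing at a visit, because the mean is then incomplete.

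**Cost.** No new data and a sentence or two of text. Compared with a pooled model that ignores pairing, the F-COPES standard error grows by √(1 + r), which is 1.10 at r = 0.2 and 1.26 at r = 0.6, so the confidence interval is somewhat wider. Moving from 62 to 30 error degrees of freedom adds about 3 % at the .01 level (critical t 2.750 against 2.657). The power statement already counts dyads and needs no change on this account.
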